### Assessment of safety

TCC is a traditional sports event in China. As it is a non-invasive intervention method and the TCC in this study is conducted under the guidance of an expert coach, its standardization and safety are sufficiently guaranteed. Nevertheless, during the study period, if the subject has any discomfort, or new changes to their condition, or any unexpected circumstances, whether related to the study or not, relevant information will be recorded in detail in the case report forms (CRFs). At the same time, researchers will identify the relevance of AEs to clinical interventions. In case of adverse reactions, the clinician will comprehensively evaluate the subject's condition and then decide whether to stop the trial. If any serious adverse event (SAE) occurs, emergency medical assistance will be sought.

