## Methods and analysis

### Study design and setting

This study will be a single-center, randomized, exploratory trial with two parallel groups. The objective is to test the comparative effects of TCC intervention and CBT protocols in improving postural balance and subjective instability feelings in patients with FAI.

We recruited subjects from the Fujian Provincial Hospital, the surrounding Sports Center, and residents of Gulou District, Fuzhou City, Fujian Province, China. Potential eligible subjects who meet the following inclusion criteria but are excluded from the exclusion criteria will be determined by two orthopedic surgeons for eventual inclusion in the study. After signing the written informed consent form, eligible participants will be randomly divided into two groups, the intervention group or the control group, at a 1:1 ratio. All assessments will be conducted at baseline, post intervention, and 3-month follow-up. This study was designed in strict accordance with the Standardized Protocol Items, including the Recommendations for Interventional Trials (SPIRIT) Checklist, and has been approved by the Ethical Committee of Fujian Provincial Hospital (no. k2019-03-035). In addition, we have completed registration in the Chinese Clinical Trials Registry in 2021. The flow diagram for this trial is shown in Figure 1. The specific flowchart of participant recruitment is shown in Table 1.

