**Figure 1 F1:**
[figure not shown]
Flow diagram of participants.

**Table 1 T1:** Trial processes chart.

**Items**	**Before enrollment−2 to 1 (week)**	**Intervention period 1−12 (week)**	**Outcome assessment 13 (week)**	**3-month follow-up**
Inclusion criteria	√			
Exclusion criteria	√			
Informed consent	√			
Baseline	√			
Randomization and allocation	√			
Intervention		√		
Static balance tests	√		√	√
Dynamic balance tests	√		√	√
CAIT	√		√	√
AOFAS-AHES	√		√	√
SF-36	√		√	√
Adverse events		√		
Reasons of drop-out and withdrawals		√		

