### Withdrawal from the study

In any of the following cases, participants will be allowed or asked to withdraw from the study:

(1) Those unwilling to continue participation in the experiment for any reason no matter at what stage of the trial.(2) Those who experience an adverse event (AE) that it is not suitable for continued participation in the trial.(3) Participants absent from TCC training too many times and not suitable for continued participation in the trial.

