### Data management and monitoring

Before the start of the trial, we will invite all researchers related to the project to participate in work training. This training mainly introduces the whole research process, including explaining the trial protocol, personnel cooperation, standard operating procedures (SOPs) of research operation, and contents of CRF and filling specifications. All experimental data will be carefully double entered into the electronic CRFs by researchers for later data statistics and analysis. To guarantee the accuracy and standardization of data entry, an independent research assistant (RA) will be responsible for managing the quality control of data collection during the trial. We will delete the identity numbers and privacy information of all participants and identify their identities using unique numerical codes to protect the privacy of all subjects. In addition, throughout the study period, the independent Data and Safety Monitoring Board (DSMB) of the Scientific Research Department of Fujian Provincial Hospital will monitor the progress of the trial, safety of the study, and integrity and authenticity of the trial. It is recommended that supervisors also should randomly check CRFs. Any incomplete data will be recorded as unknown, missing, or inapplicable. During the whole intervention process, we will record the withdrawals from the trial in detail, and the data will be recorded in CRF for later statistical analysis.

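### Adverse events and reasons for drop-out are scheduled only for weeks 1–12, so no later visit, including the 3-month follow-up, is set to collect them

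*Protocol article*

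**What the plan says.** **Length of the trial.** Study design and setting states: "All assessments will be conducted at baseline, post intervention, and 3-month follow-up". Table 1 has columns for the weeks before enrolment, the intervention (weeks 1–12), the outcome assessment at week 13, and the 3-month follow-up.

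**Adverse events.** Assessment of safety calls for a record when, "during the study period, if the subject has any discomfort, or new changes to their condition, or any unexpected circumstances" arise, whether or not they are related to the study. Data management and monitoring gives the safety board a remit with the same time reference; the clause begins "throughout the study period, the independent Data and Safety Monitoring Board (DSMB". In Table 1 the row "Adverse events" has one tick, under weeks 1–12.

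**Withdrawals.** Withdrawal from the study lists, as its first case, "Those unwilling to continue participation in the experiment for any reason no matter at what stage of the trial". On recording, Data management and monitoring says: "During the whole intervention process, we will record the withdrawals from the trial in detail". In Table 1 the row "Reasons of drop-out and withdrawals" also has one tick, under weeks 1–12.

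**Missing values.** Data management and monitoring adds: "Any incomplete data will be recorded as unknown, missing, or inapplicable". Data analysis fills missing data by last observation carried forward (LOCF).

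**The concern.** The outcome schedule runs about three months beyond the schedule for safety and withdrawal data. The Background describes sprain recurrence as common and functional ankle instability as a recurrent condition, so a new sprain after supervised training ends is a foreseeable event in either arm. If it happens in follow-up, no planned visit asks about it.

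Two uses of the data are at stake. The first is the safety information available to the monitoring board for the follow-up months. The second is the interpretation of the 3-month comparison. A participant who leaves between week 13 and month 3 has the week-13 score carried forward. The coding rule for incomplete data would show that the 3-month score is absent, but the stated recording window does not ensure that the reason is known. A reader could then not tell whether a carried-forward score belongs to someone who moved away or to someone who stopped after re-injuring the ankle.

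**Working it through.** The plan states no figure to reproduce, and the point does not depend on sample size, power or alpha. The check sets Table 1 against the text.

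**Step 1: Table 1, cell by cell.**

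| Row | Weeks 1–12 | Week 13 | 3-month follow-up |
|---|---|---|---|
| Five outcome rows (static balance, dynamic balance, CAIT, AOFAS-AHES, SF-36) | blank | ticked | ticked |
| Adverse events | ticked | blank | blank |
| Drop-out and withdrawal reasons | ticked | blank | blank |

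At the two later visits the outcome rows have 5 × 2 = 10 cells, all ticked. The safety and withdrawal rows have 2 × 2 = 4 cells, none ticked. The table therefore uses those columns where collection is planned. The two week-13 blanks matter little, because week 13 directly follows 12 weeks of recording. The substantive gap is the two blanks at 3 months.

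**Step 2: adverse events under each meaning of the study period.** The article does not define the term.

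- *It runs to the 3-month visit.* Assessment of safety then covers a sprain that a participant volunteers during follow-up, but Table 1 does not match the text and no later visit is set to ask.
- *It means the 12 training weeks.* There is some support for this. The Control group section has health education repeated monthly over the study period, and the Abstract places that education together with the 36 balance sessions inside 12 weeks. Text and table then agree, but no safety recording is planned for follow-up.

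On both readings, no visit after week 12 is scheduled to collect adverse events.

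**Step 3: withdrawals.** Table 1 and Data management and monitoring agree with each other: both refer to the intervention. Withdrawal from the study says when a person may leave, which is a different matter from when leaving is recorded. Set side by side, people can leave during follow-up, a follow-up visit is planned, and the stated recording window does not reach it.

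**Step 4: what is touched.** The section on the Cumberland ankle instability tool makes the CAIT comparison before and after treatment the primary measure. That comparison closes at week 13, so a gap that opens afterwards does not affect it. The 3-month values do depend on follow-up losses, and these are filled by LOCF.

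**The case against.** The best defence is that the article is consistent. If the study period means the 12 intervention weeks, as the health-education wording may suggest, then Assessment of safety, the board's remit and Table 1 all agree. Ending adverse-event recording when a supervised, non-invasive exercise programme ends is then a design choice. If the term is read more widely, a reported sprain is already covered by the text, and the fault is a missing tick in a summary chart. The first half of this stands: the 12-week reading is plausible and an internal contradiction on adverse events is not proven. It does not remove the point, because on that reading nothing is planned for follow-up at all.

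A reader might also infer that the withdrawal rule and the recording sentence contradict each other. They do not. One concerns the right to leave and the other the record, and the recording sentence does not say that it stops at week 12. The supportable statement is that the window named in the text and in Table 1 is too short for the trial's length.

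It is fair, too, that the participant flow diagram, the standard operating procedures and the instructions for completing the case report form are not shown and may cover later losses. That limits certainty. But the article is not silent on timing: it names a window in two places, and that window stops short of the last visit.

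Finally, LOCF is applied whatever the reason for leaving, so recorded reasons would not change the planned 3-month estimate. That stands. They would change only how the estimate can be read.

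**Conclusion.** The point holds as a minor one: the recording window is fixed too short for a trial that assesses outcomes to three months. As written, no visit after week 12 is set to collect adverse events or reasons for withdrawal, whichever meaning of the study period is intended.

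The size is best stated as two unticked rows at one important visit, plus two blanks of little weight at week 13. No size of harm can be given. The article offers no re-sprain rate for the follow-up months and does not split expected withdrawals by period. A reader might infer that the 3-month result is biased by some amount, or that events will certainly be lost. The documents support neither; they support only that such events and reasons may go unrecorded.

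The conclusion assumes that Table 1 shows the intended collection schedule and that the documents not shown do not extend it.

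**What to change.** 1. State under Assessment of safety that the study period runs to the 3-month visit.
2. In Table 1, tick the adverse-event row and the drop-out row at week 13 and at the 3-month follow-up.
3. In Data management and monitoring, change the withdrawal sentence so that withdrawals and their reasons are recorded through the last follow-up visit.
4. At both visits, ask both arms the same question about new ankle sprains since the previous visit. Report the answers descriptively by arm as safety data, not as an added endpoint.

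The cost is four table cells, two edits to the text and one case report form item at two visits that already take place. The downside is recall over about three months, so the dates of minor sprains will be approximate. The change does not repair LOCF, which remains a separate matter; it only lets a reader see why a 3-month value had to be filled.

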### Data management and monitoring

Before the start of the trial, we will invite all researchers related to the project to participate in work training. This training mainly introduces the whole research process, including explaining the trial protocol, personnel cooperation, standard operating procedures (SOPs) of research operation, and contents of CRF and filling specifications. All experimental data will be carefully double entered into the electronic CRFs by researchers for later data statistics and analysis. To guarantee the accuracy and standardization of data entry, an independent research assistant (RA) will be responsible for managing the quality control of data collection during the trial. We will delete the identity numbers and privacy information of all participants and identify their identities using unique numerical codes to protect the privacy of all subjects. In addition, throughout the study period, the independent Data and Safety Monitoring Board (DSMB) of the Scientific Research Department of Fujian Provincial Hospital will monitor the progress of the trial, safety of the study, and integrity and authenticity of the trial. It is recommended that supervisors also should randomly check CRFs. Any incomplete data will be recorded as unknown, missing, or inapplicable. During the whole intervention process, we will record the withdrawals from the trial in detail, and the data will be recorded in CRF for later statistical analysis.

### Data analysis

Statistical analysis will be carried out using SPSS Statistics, version 22.0 (SPSS Inc., Chicago, IL, USA). All assigned subjects with available data will be analyzed according to the intention-to-treat principle. Continuous variables, such as CAIT score, age, and disease duration, will be expressed as mean ± standard deviation (SD) or medians (25th to 75th centiles), depending on whether the distribution of variables is normal or skewed. For other categorical data, we will use Mann–Whitney test, chi-square test, or Fisher's exact test for statistical analysis as appropriate. Multiple-measure variables will be analyzed by repeated-measures ANOVA. Additionally, we will use the last-observation-carried-forward method to deal with the missing data. Statistical significance will be assessed as *p* < 0.05.

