### Sample size

Sample size calculations were done using the G-power 3.1.9.2 software (developed by the University of Düsseldorf, Germany). An effect size of 0.8 and a two-sided alpha level of 0.05 were set based on the differences of pre- and post-treatment repeated measurement points of Star Excursion Balance Test (SEBT) and CAIT; a total sample of 56 participants (28 patients in each group) is required to achieve 90% power. The estimated withdrawal rate was 10–20%, and a total of 68 participants (34 patients in each group) were planned to be enrolled in this clinical trial. The power analysis is based on the primary outcome variable, including within-group differences in SEBT and CAIT (dependent variables) before and after treatment. The means and standard deviations of the SEBT and CAIT are based on the results from a similar published study from Spain (18) and preliminary experiment of the research group (intervention group: ▴SEBT-posteromedial M = 6.46, SD = 6.89, ▴CAIT M = 10.8, SD = 2.21, control group: ▴SEBT-posteromedial M =0.64, SD = 3.86, ▴CAIT M =0.2, SD = 2.10), with a 1:1 allocation ratio.

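### LOCF as the only missing-data method scores anyone lost before week 13 as unchanged, which biases the TCC–CBT comparison if participants improve and can cost power if both arms do

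*Protocol article*

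**What the plan says.** The Data analysis section fixes three things. The analysis set is "All assigned subjects with available data will be analyzed according to the intention-to-treat principle". The model is given as "Multiple-measure variables will be analyzed by repeated-measures ANOVA". For missing values, "we will use the last-observation-carried-forward method to deal with the missing data". No reason is given for that choice and no alternative is named.

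The schedule comes from Study design and setting: "All assessments will be conducted at baseline, post intervention, and 3-month follow-up". Table 1 confirms that no outcome is measured during weeks 1–12. The Sample size section expects losses: "The estimated withdrawal rate was 10–20%, and a total of 68 participants (34 patients in each group) were planned".

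Three other places matter:
- The Background and the Discussion both hypothesise significant improvement in both arms, with TCC possibly better.
- Withdrawal from the study includes a criterion for too many absences, and it names TCC training only.
- The CAIT section makes the before–after comparison of CAIT the primary measure of functional improvement, with a minimum detectable change of 3 points or more.

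**The concern.** With three visits, LOCF leaves little room for interpretation. Someone with no week-13 value has only the baseline to carry forward, so the imputed change is zero at week 13 and at 3 months. If both programmes work as the protocol expects, zero is the wrong value in both arms.

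Two consequences follow for the main comparison. First, if drop-out differs between arms, the difference in drop-out is converted into an apparent treatment difference. The absence criterion that names only TCC makes unequal loss plausible. Second, even with equal drop-out, a cluster of zeros among participants who otherwise improved pulls the arms together and widens the spread. Imputed values are also treated as if they had been observed.

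**Working it through.** **The plan's own figure.** The Sample size section says "An effect size of 0.8 and a two-sided alpha level of 0.05 were set" and that "a total sample of 56 participants (28 patients in each group) is required to achieve 90% power". By the two-sample t calculation, 28 per arm gives 83.6% power two-sided, and 34 per arm are needed for 90% (90.2%). The stated 56 is reproduced only one-sided (90.5%). That is a separate point. It matters here because 34 per arm reaches 90% only with no loss, so there is no reserve to absorb a diluted effect.

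**Inputs from the protocol.** 34 per arm; 10–20% withdrawal (about 3 to 7 of 34); CAIT change 10.8 (SD 2.21) for intervention and 0.2 (SD 2.10) for control; SEBT posteromedial change 6.46 (SD 6.89) and 0.64 (SD 3.86).

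**Inputs assumed.** Drop-out by arm, all of it before week 13 and at random; the gain under CBT; a common SD of 2.2 unless stated. The protocol gives no CBT-specific gain and no arm-specific drop-out. The test is a two-sample t-test on change to week 13, not the full group-by-time ANOVA.

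**Formulas.** With drop-out p, true mean change m and SD s in an arm:
- LOCF mean change = (1 − p) × m
- LOCF variance = (1 − p) × s² + p × (1 − p) × m²

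**Step 1: equal drop-out.** The difference becomes (1 − p) × (true difference). A true 1.72 points becomes 1.55 at 10% loss and 1.38 at 20%.

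**Step 2: unequal drop-out, no true difference.** Bias = −(p_TCC − p_CBT) × gain. Simulated at 34 per arm with 20% TCC and 10% CBT loss:

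| Common gain (points) | Bias | False-positive rate |
|---|---|---|
| 3 | −0.1 × 3 = −0.3 | about 8% |
| 6 | −0.1 × 6 = −0.6 | about 13% |
| 10.8 | −0.1 × 10.8 = −1.1 | about 17% |

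Observed cases give about 5% in each row. Reversing the drop-out rates reverses the sign. With 17% against 13% loss and a gain of 10.8, the bias is −0.04 × 10.8 = −0.43 and the rate about 7%. With equal 15% loss it stays at 5%.

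**Step 3: power, true difference 0.8 SD (0.8 × 2.2 = 1.76 points), 15% loss in each arm.** Take TCC 10.8 and CBT 9.04:
- LOCF means: 0.85 × 10.8 = 9.18 and 0.85 × 9.04 = 7.68, so the difference is 1.50.
- LOCF SDs: √(0.85 × 4.84 + 0.1275 × 116.64) = 4.36 and √(0.85 × 4.84 + 0.1275 × 81.72) = 3.81, pooled 4.09.
- The standardised difference falls from 0.80 to 1.50 / 4.09 = 0.37.

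| TCC gain | CBT gain | SD | LOCF power | Observed cases |
|---|---|---|---|---|
| 10.8 | 9.0 | 2.2 | 33% | about 85% |
| 6 | 4.2 | 2.2 | 60% | about 85% |
| 3 | 1.2 | 2.2 | 80% | about 85% |
| 1.96 | 0.2 | 2.2 | 83% | about 85% |
| 6 | 2 | 5 | 81% | about 85% |
| 10.8 | 6.8 | 5 | 69% | about 84% |

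**Step 4: the planning figures as written.** At 10% / 20% loss, CAIT power is 100% either way. SEBT power is 97.6% / 95.3% under LOCF against 97.8% / 96.2% for observed cases.

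**Step 5: the 3-month visit.** Early leavers sit at baseline, which lowers the 3-month mean if participants improve. Late leavers are recorded as having no change since week 13. No size can be given, because the protocol states no expected course after week 13.

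**The case against.** The strongest reply is that the damage depends on inputs the protocol does not contain. Withdrawal is given as one overall rate, and with equal loss and no true difference the false-positive rate stays at 5%. The larger power losses need a substantial CBT gain, large relative to the SD of change. With the protocol's own control change of 0.2 points, LOCF costs one percentage point or less (Step 4). This stands, and it limits what can be said about size. It does not remove the defect: the comparator is an active programme that the protocol expects to work, and the difference is still attenuated when drop-out is equal.

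A reader might go further and infer that LOCF overstates durability. The documents do not support this. It would do so only if effects wane after week 13, which is not stated. With continued improvement it would understate durability, and early leavers held at baseline lower the 3-month mean.

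A reader might also see a contradiction between LOCF and the restriction to subjects with available data. The phrase can mean everyone with at least a baseline value, later visits being filled in, and the two are then compatible.

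Finally, the trial is described as exploratory, and detailed sensitivity analyses can be left to an analysis plan. That is fair, but LOCF itself is a choice this document has already made.

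**Conclusion.** The concern holds in conditional form. LOCF is fixed as the sole method and, on this visit schedule, imputes zero change for early leavers in a trial that expects improvement in both arms.

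The between-arm difference shrinks by 10–20% if losses are equal, random and before week 13. If losses are unequal, it shifts in either direction by roughly the drop-out difference times the gain. The false-positive rates of 8–17% rest on an assumed 20% against 10% loss and SD 2.2.

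It would be too strong to say that LOCF cuts power sharply in this trial. The fall to 60% or 33% needs CBT gains of 4.2 or 9.0 points with SD 2.2. It is negligible if CBT hardly changes, and small when the SD of change is large relative to the gains. The mechanism is certain; its size is not known from the protocol.

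**What to change.** Remove LOCF as the primary method. Analyse all randomised participants with a likelihood-based mixed model using every observed value: in SPSS MIXED, group, visit, group-by-visit and baseline value, with unstructured covariance. State that the analysis set is all randomised participants, so that the phrase about available data cannot be read as a restriction. Keep LOCF at most as a sensitivity analysis. A multiple-imputation analysis with a delta shift by arm is a useful option but can be left to the analysis plan.

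The cost is a change of wording and slightly more analysis work; visits, recruitment and software stay the same. The model relies on data being missing at random, and participants with no post-baseline value add little or nothing to the treatment contrast. The change should be made before treatment allocation is revealed to the statisticians.
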